**Methods:**

This cluster randomised controlled trial will be a 6-week community-based intervention programme for older people aged 60 years and above from urban poor settings. A minimum of 164 eligible participants will be recruited from 8 clusters (low-cost public subsidised flats) and randomised to the intervention and control arm. This study will be underpinned by the Health Belief Model with an emphasis towards self-efficacy. The intervention will comprise multicomponent group exercise sessions, nutrition education, oral care education and on-going support and counselling. These will be complemented with a kit containing practical tips on exercise, nutrition and oral care after each session. Data will be collected over four time points; at baseline, immediately post-intervention, 3-months and 6-months follow-up.

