### Sample size

The sample size has been estimated for the primary outcome of this study, that is, changes in physical function. The sample size calculation is estimated based on several measures of physical function including mobility, balance, stability (8-Foot Up and Go Test), aerobic endurance (6-minute walk test) and activities of daily living (ADL). In order to achieve 80% power to detect differences in the 8-Foot Up and Go Test, 6-minute walk test and ADL as previously reported [27,64,65], an individually randomised trial would require 45 participants per arm. With a hypothesised intra-cluster correlation coefficient (ICC) of 0.02 and a minimum of 20 participants recruited per cluster, the required sample size is 63 per arm. Assuming 30% loss to follow-up, 82 participants per arm or a minimum total of 164 participants will be required. To recruit at least 164 participants with a cluster size of approximately 21, it will be necessary to recruit 8 low-cost flats.

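### The 30% loss allowance is computed as 63 × 1.3 = 82 per arm instead of 63 / 0.70 = 90, so on the plan's own steps 82 recruited leaves about 57 per arm, not 63

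*Protocol article*

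**What the plan says.** The calculation is in the protocol article under Methods, Sample size, and runs in three steps.

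- The starting point is 80% power on three measures of physical function, for which "an individually randomised trial would require 45 participants per arm".
- Clustering is allowed for with a "hypothesised intra-cluster correlation coefficient (ICC) of 0.02" and "a minimum of 20 participants recruited per cluster", after which "the required sample size is 63 per arm".
- Attrition comes last: "Assuming 30% loss to follow-up, 82 participants per arm or a minimum total of 164 participants will be required".

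The section then turns this into flats: "To recruit at least 164 participants with a cluster size of approximately 21, it will be necessary to recruit 8 low-cost flats". The Methods paragraph of the abstract repeats the total as the headline figure: "A minimum of 164 eligible participants will be recruited from 8 clusters". The section on randomisation and allocation concealment fixes four flats per arm.

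**The concern.** An allowance for attrition has to start from the number still needed at the end and divide by the proportion expected to remain. Adding 30% of the final number is a different operation, because the 30% who are lost come out of the larger, recruited group. The gap between the two methods widens as the loss grows, and at 30% it is no longer a rounding matter.

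At stake is whether the stated minimum meets the requirement printed just before it. The 164 is the figure readers will take from the abstract. If loss reaches the planned 30% and the result is null, they will judge the trial against a completer number that the stated size was never going to deliver.

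**Working it through.** **Inputs, all from the protocol article.** 45 per arm under individual randomisation, ICC 0.02, at least 20 recruited per flat, 63 per arm after clustering, 30% loss, 82 per arm (164 in total), and about 21 per flat in 8 flats (Sample size); 4 flats per arm (Randomisation and allocation concealment).

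**Step 1: reproduce the 63.** Design effect = 1 + (m − 1) × ICC.
- m = 20: 1 + 19 × 0.02 = 1.38, and 45 × 1.38 = 62.1, rounded up to 63.
- m = 21: 1 + 20 × 0.02 = 1.40, and 45 × 1.40 = 63.0.

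The 63 reproduces, using the recruited cluster size.

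**Step 2: reproduce the 82.**
- Multiplying: 63 × (1 + 0.30) = 81.9, rounded up to 82. This matches.
- Dividing: 63 / (1 − 0.30) = 90.0. This does not match.
- Order of operations: inflating 45 by 1 / 0.70 before applying a design effect of 1.38 or 1.40 gives 88.7 to 91, depending on rounding. This does not match either.

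At the plan's cluster size of 20 to 21, only multiplication by 1.3 leads to 82.

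**Step 3: what 82 delivers at 30% loss.**
- Remaining: 82 × 0.70 = 57.4 per arm, which is 5.6 (about 9%) short of 63.
- Loss that 82 can absorb while keeping 63: 1 − 63/82 = 23.2%.
- With 8 × 21 = 168 recruited: 84 × 0.70 = 58.8 per arm, still below 63; the tolerable loss is 1 − 63/84 = 25%.

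**Step 4: effect on power.** The article gives no effect size and no sidedness. I assume a two-sided 5% test and the standardised difference d that gives 80% power with 45 per arm. By the normal approximation, d = (1.960 + 0.842) × √(2/45) = 0.591. Effective size = completers / design effect, and power = Φ(d × √(n_eff/2) − 1.960).

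| Recruited per arm | Completers per arm | Cluster size in design effect | Design effect | Effective n per arm | Power |
|---|---|---|---|---|---|
| 82 | 57.4 | 57.4 / 4 = 14.35 (retained) | 1.267 | 45.3 | 80.3% |
| 84 | 58.8 | 58.8 / 4 = 14.7 (retained) | 1.274 | 46.2 | 81.0% |
| 82 | 57.4 | 20 (recruited) | 1.38 | 41.6 | 76.8% |
| 82 | 57.4 | 21 (recruited) | 1.40 | 41.0 | 76.2% |

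**Step 5: the size the plan's inputs imply on retained clusters.** Let k be the number retained per flat. Four flats per arm must satisfy 4k = 45 × [1 + (k − 1) × 0.02], so 4k = 44.1 + 0.9k and k = 44.1 / 3.1 = 14.23. Recruitment per flat is 14.23 / 0.70 = 20.3, or 81.3 per arm, rounded up to 82.

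**The case against.** The strongest reply is that 164 is enough. The variance inflation at analysis depends on how many people per flat are analysed, and attrition shrinks that number. With four flats per arm and 30% loss there are about 14 per flat, the design effect falls to 1.267, and Step 5 gives 82 per arm directly. This reply stands, and it settles the size of the problem. It does not rescue the printed text. The section ties its design effect to participants recruited per flat, calls the resulting 63 the requirement and inflates that 63. On the retained-cluster route the requirement would be 45 × 1.267 = 57.0 completers, and 63 would not appear.

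Two stronger readings are tempting. A reader might infer that power falls to 76–77%. That figure keeps a design effect for 20 to 21 per flat while analysing 14.35 per flat, two inputs that cannot both hold with four flats per arm. A reader might also infer that the trial should have recruited 180. That is what the printed chain gives, but 90 recruited would leave 63 at 15.75 per flat, an effective 48.6 per arm and about 83% power, more than the plan asks for.

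It can also be said that completers are not the exact analysis denominator. The Statistical analysis section plans generalised estimating equations and mixed models over three post-baseline visits, so a participant lost late may still contribute, and the article does not say to which visit the 30% refers. That is fair. It makes the power figures illustrative, but it does not change the attrition arithmetic.

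**Conclusion.** The attrition step is wrong as printed: 82 per arm does not leave the stated 63 after 30% loss. It leaves 57.4 and is consistent with a loss of at most 23%. This part rests only on figures in the article.

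No loss of power is demonstrated. With the design effect taken on retained clusters, 164 recruited supports about 80% power at 30% loss. That statement assumes a two-sided 5% test, an effect calibrated to 80% power at 45 per arm, an ICC of 0.02 and equal retention across flats. It makes no correction for having only four clusters per arm, a limitation that the Discussion acknowledges in general terms. The point is minor: a stated figure that does not follow from its stated requirement, together with silence on which cluster size the design effect should use once dropout is allowed for.

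**What to change.** Reword the attrition sentence under Sample size in one of two ways.

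- Keep the 63 and say that 164 recruited leaves 63 per arm only if loss is at most 23%.
- Or re-derive the size on retained clusters: about 14.35 per flat at 30% loss, design effect 1.267, effective size about 45.3 per arm, and hence about 80% power before any small-cluster correction.

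In either case, state whether the design effect uses recruited or retained cluster size. The second option is the more useful, because it keeps the 30% loss assumption and supports the existing total.

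The cost is a sentence or two. The Study status section reports that screening and baseline are complete, and neither option calls for further recruitment or any change to design or analysis. The 164 in the abstract can stay once its justification is corrected.

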### Process evaluation

A range of process data will be conducted to complement the outcome data. Process measures will include participants’ attendance at exercise and training sessions, participants’ satisfaction with all three intervention components (group exercise session, therapeutic lifestyle training focusing on nutrition and oral care and on-going tailored motivation support). Participants’ general satisfaction with the program, intensity, duration and pace of the program will be evaluated.

A formal effectiveness evaluation will be conducted via focus-group discussions with key stakeholders, including cluster community leaders, study co-ordinators, project officers and study participants after the intervention to assess the implementation of the intervention, to evaluate the sustainability and identify enablers and barriers. In addition, a cost-effectiveness of the intervention will be evaluated based on the total cost of the intervention and the number of participants.

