Nutrition is an integral part of health and well-being throughout life and is linked to the independence and quality of life of older individuals [38]. Appetite loss, sensory deficit, mastication problems, poor oral health and gastrointestinal disorders often result in inadequate food intake and poor nutrient absorption [39]. Malnutrition among the aged is a major concern and is associated with a progressive decline in health, loss of independence, increased length of hospital stay and readmissions, healthcare costs, fall risks, delayed wound healing, poorer quality of life and mortality [39,40]. The nutritional status of older people is further exacerbated by unintentional weight loss, limited mobility, loneliness, neglect, economic constraints, presence of multi-morbidities and polypharmacy [41]. Nutritional screening among the elderly is useful to identify those at risk of malnutrition who may benefit from appropriate interventions [42]. Nutrition education and counselling interventions involving active participation, goal setting, self-efficacy and peer support has yielded promising results in community-dwelling older adults [43]. The World Health Organization Global Oral Health Programme has also called for oral health promotion among older people to improve their nutritional status and quality of life [44].

Maintaining adequate levels of physical activity and sustaining an appropriate diet are important to minimise the adverse physiological changes associated with aging. Optimal multicomponent exercise and lifestyle interventions to improve physical function and maintain independence among older people in low-resource settings particularly in Asian populations have yet to be established. To address this gap, this study aims to develop and evaluate the effectiveness of a multiComponent Exercise and theRApeutic lifeStyle (CERgAS) intervention program targeted at improving physical performance and maintaining independent living as compared to general health education among older people in an urban poor setting. This study also seeks to identify the subgroup of older people that will benefit the most from this intervention.

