#### General health status

A face-to-face interview will be conducted to obtain information about participants’ demographics, medical history, falls history, falls efficacy scale (FES-I) [49], cognitive assessment (Mini Mental State Examination (MMSE)) [50], quality of life assessments (SF-12) [51,52], depressive symptoms (Geriatric Depression Scale (GDS) [53]), social support (DUKE Social Support Index [54] and Lubben Social Network Support-6 (LSNS-6) [55]), physical activity (Physical Activity Scale for the Elderly (PASE)) [56], pre-activity readiness questionnaire measured though PAR-Q+ questionnaire [57], stage of motivational readiness for change using the Physical Activity Stages of Change Questionnaire [58], activities of daily living (Katz-ADL) [59] and Lawton’s Instrumental Activities of Daily Living (IADL) [60], nutrition status (Mini Nutritional Assessment (MNA)) [61] and oral health (Geriatric Oral Health Assessment Index (GOHAI)) [62].

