### Control group

Participants in the control arm will be provided with a general health education booklet containing information on healthy lifestyle. Participants will be given the similar number of contact hours with different contents not related to physical activity, nutrition or motivation towards healthy living and will be advised to maintain their current level of physical activity.

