### Outcomes

#### Primary and secondary outcomes and measurements

The primary outcome of the study is improvement in physical performance among older people assessed by ADL and IADL, grip strength and gait speed. Secondary outcomes will include body composition analysis using BIA along with other measurements consisting of pre-activity readiness for physical activity (PAR-Q+), Physical Activity Scale for the Elderly (PASE), quality of life (SF-12), Falls Efficacy Scale-International (FES-I), fear of falling, depression (GDS), cognitive function (MMSE), nutrition status (MNA) and oral health (GOHAI).

Adverse events will be monitored by the team at the end of each session. Every week participants will fill in a form to indicate if they developed pain, muscle soreness as well as significant injuries or a medical event that results in participant seeking medical attention from a healthcare professional. If participants develop any acute symptoms or any serious adverse events and their condition becomes too serious for the medical doctor in the research team to manage in a community setting, they will be immediately referred and brought to the nearest hospital.

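### The economic evaluation labelled cost-effectiveness rests on total intervention cost and a head count, which can give only a cost per participant

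*Protocol article*

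**What the plan says.** The only sentence in the protocol article on an economic evaluation closes the Process evaluation section: "a cost-effectiveness of the intervention will be evaluated based on the total cost of the intervention and the number of participants". The Statistical analysis section adds nothing on costs.

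Three other places bear on it:

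- **Comparator.** The Background sets the aim as "improving physical performance and maintaining independent living as compared to general health education among older people in an urban poor setting". Under Control group, that arm receives a health education booklet, and "Participants will be given the similar number of contact hours with different contents". Delivering the control programme therefore uses resources.
- **Outcomes.** The primary outcome is "improvement in physical performance among older people assessed by ADL and IADL, grip strength and gait speed". These are compared between arms, with baseline adjustment, under Statistical analysis.
- **Numbers.** The Sample size section concludes that "82 participants per arm or a minimum total of 164 participants will be required".

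Nothing in the article links the outcomes or the control arm to the cost evaluation.

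**The concern.** Cost-effectiveness relates what is spent to what is gained, relative to an alternative. It needs a cost difference between arms and an outcome difference between arms. The stated basis has neither. The number of participants measures reach, so for a given total cost the figure improves simply by enrolling more people, even if none of them benefits.

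What is at stake is the meaning of one reported number. A reader who sees a result called cost-effectiveness will take it to say something about value for money against general health education. Built from the stated inputs, it could not separate a useless programme from an effective one.

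**Working it through.** The article gives no cost, effect or ratio for this item, so there is no stated figure to reproduce. The check asks whether the two named ingredients can respond to the quantities that a cost-effectiveness measure must depend on.

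**Inputs from the article**

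- Ingredients of the evaluation: "the total cost of the intervention and the number of participants" (Process evaluation). Write these as C and n.
- n = 82 per arm or 164 in total (Sample size). The sentence does not say which participants are counted.

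**Assumptions, for illustration only**

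- C = 10,000 currency units.
- Control delivery cost K = 0 or 5,000.
- Between-arm gait-speed effect E = 0, 0.05 or 0.10 m/s.

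**Formulas**

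- From the named ingredients: C / n. The article says that the evaluation is based on the two quantities and does not write a division. Division is the natural reading, and no other combination of C and n would bring in an outcome.
- Incremental ratio, with 82 per arm: ((C − K) / 82) / E.

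**Results**

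| E (m/s) | K | C / 82 | Incremental ratio (per m/s) |
|---|---|---|---|
| 0 | 0 | 122.0 | undefined |
| 0 | 5,000 | 122.0 | undefined |
| 0.05 | 0 | 122.0 | (10,000 / 82) / 0.05 = 2,439 |
| 0.05 | 5,000 | 122.0 | (5,000 / 82) / 0.05 = 1,220 |
| 0.10 | 0 | 122.0 | (10,000 / 82) / 0.10 = 1,220 |
| 0.10 | 5,000 | 122.0 | (5,000 / 82) / 0.10 = 610 |

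The middle column never moves. With n = 164 it is 10,000 / 164 = 61.0, again whatever the effect. Counting the control participants thus halves the figure without adding any control cost or control outcome. At C = 50,000 (K = 0 or 25,000) every value is five times as large and the pattern is the same. The invariance needs no assumed value, because E and K do not appear in C / n.

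**The case against.** The best defence is that this is one sentence in a journal article that condenses a fuller protocol. Perspective, time horizon, costing method and handling of uncertainty are commonly left to a separate plan, and the outcomes and between-arm comparison are defined elsewhere in the article. That is fair, and the absence of those details is not a fault here. It does not rescue the sentence, however, because the sentence does not merely leave the basis unsaid. It states a basis, and that basis does not fit the label.

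It can also be argued that the control contact hours serve to match attention, and that a policy maker choosing between this programme and nothing may not want their cost deducted. With similar contact hours in both arms, deduction could make the programme look almost free. This is a real choice. It is a reason to state the comparator openly; the trial's own stated comparator is general health education.

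Three stronger readings are tempting and should not be drawn:

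- **That control costs are counted as zero.** The article assigns the control arm no cost, zero or otherwise. Those costs are left out of the stated basis.
- **That policy makers will be handed a misleading figure.** The Abstract and the Discussion speak of informing health policy, but neither mentions cost. The main Discussion makes that use conditional on significant positive effects, and any cost figure would presumably appear beside the effect estimates.
- **That quality-adjusted time is available because SF-12 is collected.** It would need a utility derivation, which the article does not describe.

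**Conclusion.** The point holds as an error in a stated rule. Followed as written, the Process evaluation sentence gives at most an average cost per participant. That average carries no information on effect and none on the comparison with general health education, so it should not be called cost-effectiveness. It is also ambiguous by a factor of two (164 / 82) until the participants counted are named.

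The conclusion rests on reading the two named quantities as the whole basis of the calculation, which is what the sentence says. If a fuller economic plan defines an outcome and a comparator, the article's sentence misdescribes that plan and still needs correcting. The currency amounts above are assumed and show only the pattern.

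The consequence is limited. The item belongs to the process evaluation, is neither a primary nor a secondary outcome, and does not touch randomisation, sample size or the primary analysis.

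**What to change.** Choose one of two options and write it down before outcome data are examined.

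1. **Keep the cost-effectiveness claim.** Define it as incremental delivery cost per participant (intervention minus control, including the control sessions and booklet) per unit of the adjusted between-arm difference in one named outcome already collected, such as gait speed. Give uncertainty that respects the eight flats, four per arm. Because the ratio is undefined at zero effect, also report the cost difference and the outcome difference separately. Do not offer a quality-adjusted version from SF-12 unless the utility derivation is specified.
2. **Claim less.** Rename the item cost per participant, say whether the denominator is the intervention arm or everyone, and drop the cost-effectiveness wording.

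Option 2 changes one sentence and needs no new data. Option 1 adds a small costing task and one analysis. The outcome data are already planned, but control-arm delivery costs would be new. Study status reports that the intervention is already running, so some of those costs may have to be reconstructed, and recording should start promptly.

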### Statistical analysis

The study design provides for four assessments with study participants – at baseline, immediately post-intervention, three months and six months follow-up. Description of participants’ baseline characteristics will be reported by groups. Categorical variables will be summarised by frequencies and percentages. Continuous variables will be summarised by means and SD or non-parametric equivalents. The data analysis for this trial will be undertaken on an intention-to-treat (ITT) principle [66]. The continuous variable outcomes (immediately post-intervention, three months and six months) will be compared between groups using a generalised estimating equations and linear mixed effect models with adjustment for baseline covariates. Groups with dichotomous outcomes will be compared using logistic regression models. Baseline values will be entered as covariates. Statistical significance is set at p < 0.05 and mean 95% confidence intervals (CI) or differences in percentage between the two groups will be reported at the follow-up time points. Data will be entered and analysed with SPSS 22.0 (SPSS Inc., Chicago, IL, USA).

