### Randomisation and allocation concealment

Randomisation takes place at the cluster level, that is, the low-cost public subsidised flats, to avoid contamination. The eight housing projects will be randomised into the intervention arm (4 flats) and control arm (4 flats). The study statistician using a computer generated random number sequence will allocate the low-cost flats into the intervention and control group. The statistician using sealed envelopes will advise the study coordinator of the low-cost flats allocation. Allocation will be concealed from the research team recruiting the flats and participants, as randomisation will only take place after baseline measures have been accomplished.

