## Discussion

There is an urgent need for locally acceptable sound interventions to promote healthy aging among older Malaysians. The CERgAS trial presents a unique approach, delivering a multicomponent intervention to older adults aged 60 years and older in an Asian urban poor setting. Furthermore, this study is an important step forward and contributes to establishing the effectiveness of a multicomponent exercise and therapeutic lifestyle intervention to increase physical activity and improve nutrition status among community-dwelling older adults. In addition, the demographics of participants who attend the study will be identified and the extent of acceptance towards the intervention according to demographic characteristics such as gender, age and ethnicity will be examined. Moreover, this community-based lifestyle intervention will be conducted in a naturalistic setting, allowing participants to integrate changes into their daily lives in a real-life context. This implies that the intervention delivered can be potentially transferable to other community settings. The process evaluation will provide insight as to how the findings can be extrapolated to urban and rural settings.

While every effort will be made to maximise participation rates in each cluster, this study is limited by the small number of clusters involved in the study and may present as confounding issues during the analyses.

Improved gait speed, muscle strength, quality of life, ADLs and reduced falls accrued from regular participation in exercise and physical activity are anticipated. Adopting a healthy and nutritious diet along with good oral health will likewise improve nutritional status, functional ability and ultimately enhance their quality of life. Finally, the on-going motivational support will provide the elderly adults with the support and encouragement needed to reach their goals, identify barriers and suggest ways to overcome obstacles in efforts to increase their self-efficacy towards healthier aging. To encourage adherence in the intervention, each component (exercise, nutrition and oral care) will be designed to be interactive, enjoyable and manageable.

If the intervention produces significant positive effects, the findings will provide valuable evidence and serve as a model to inform health policies and identify locally acceptable strategies to promote healthy aging and prevent and delay functional decline among older Malaysians.

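### GEE and mixed models are named side by side for eight randomised flats, with no deciding model and no statement that flat is the cluster; standard uncorrected GEE would test at about 14%, not 5%

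*Protocol article*

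**What the plan says.** In the protocol article, Statistical analysis, the continuous outcomes at the three follow-up times "will be compared between groups using a generalised estimating equations and linear mixed effect models with adjustment for baseline covariates". The same section adds that "Statistical significance is set at p < 0.05" and that 95% confidence intervals will be reported. Neither method is called primary. Flats are not mentioned in the section, either for these models or for the logistic regression planned for dichotomous outcomes.

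Under Randomisation and allocation concealment, eight housing projects are allocated, four to each arm. Under Sample size, the clustering is recognised: an ICC of 0.02 with at least 20 people in each flat raises the requirement to 63 in each arm. The Discussion concedes that "this study is limited by the small number of clusters involved in the study", but describes the consequence as possible confounding, not as a problem for standard errors or tests.

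**The concern.** The arm effect is a comparison between flats, and eight flats in two arms leave 8 − 2 = 6 degrees of freedom for it. The robust standard error of GEE is justified for many clusters. With four per arm it is too small on average, and the usual normal reference makes the test more liberal still. Naming GEE on equal terms with a mixed model therefore leaves open a route whose p-values and intervals can be seriously optimistic. Because the section does not name flat as the cluster, it also leaves open a model that handles only the repeated visits. At stake is whether a positive result at 5% can be relied on, in a trial meant to inform health policy.

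**Working it through.** **Inputs.** Eight flats, 4:4 (Randomisation and allocation concealment). ICC 0.02, at least 20 participants per flat, 45 per arm under individual randomisation, 80% power, 30% loss (Sample size). Alpha 0.05 (Statistical analysis). A two-sided test is assumed, as the article does not say. With 30% loss, 20 × 0.7 = 14 complete per flat.

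**The plan's own figure.** Design effect = 1 + (20 − 1) × 0.02 = 1.38, and 45 × 1.38 = 62.1, rounded up to 63 per arm. This reproduces, so the design does allow for correlation within flats.

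**Step 1: GEE, equal flats.** With four flats per arm, the uncorrected sandwich divides the squared deviations of the flat means by 4, where an unbiased variance divides by 3. Its variance is therefore 3/4 of what it should be.
- Unbiased between-flat variance, normal critical value: P(|t6| > 1.96) = 9.8%.
- Uncorrected sandwich, normal critical value: P(|t6| > 1.96 × √0.75) = P(|t6| > 1.697) = 14.1%.
- Uncorrected sandwich, t6 critical value: P(|t6| > 2.447 × √0.75) = P(|t6| > 2.119), about 8%. Changing the reference alone is not enough; the variance needs correcting too.

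These results do not depend on the ICC.

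**Step 2: flats ignored.** The size is P(|Z| > 1.96/√DE). With 14 per flat, DE = 1 + 13 × 0.02 = 1.26 and the size is 8.1%. With 20 per flat, DE = 1.38 and the size is 9.5%.

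**Step 3: mixed model with a random flat effect, equal flats.** Let MSB and MSW be the between-flat and within-flat mean squares. If MSB > MSW, the REML test uses MSB on 6 df. Otherwise the flat variance is estimated as zero, and the pooled variance is used on about n − 2 df. Drawing these mean squares under no effect (400,000 draws, ICC 0.02, 14 and 20 per flat) gives:
- normal reference: 5.6% and 6.2%;
- Satterthwaite df: 4.0% and 4.3%;
- df fixed at 6: 1.9% and 2.2%.

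**Step 4: simulation of fitted models.** No effect, baseline-adjusted, one follow-up time, ICC 0.02, 4,000 trials per cell (Monte Carlo error about 0.4 to 0.6 points). The unequal sizes are an assumption.

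| Test | 20 per flat | 14 per flat | flats of 10 to 40 |
|---|---|---|---|
| GEE, uncorrected, z | 14.8% | 15.4% | 20.4% |
| GEE, uncorrected, t6 | 8.7% | 9.2% | 12.9% |
| Flats ignored | 10.3% | 8.6% | 10.0% |
| Mixed model, z | 6.8% | 6.2% | 6.0% |
| Mixed model, df fixed at 6 | 2.5% | 2.1% | 2.2% |
| Cluster-level t-test, 6 df | 5.8% | 5.5% | 4.9% |

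Over ICC 0 to 0.10 with equal flats, uncorrected GEE stays between 13.2% and 15.7%, while the mixed model with z ranges from 3.8% to 9.7%.

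**Step 5: choosing the smaller p-value.** With equal flats the sandwich variance (0.75 × MSB) is always below the mixed-model variance, so GEE always gives the smaller p-value under a common reference. Picking the better of the two gives 14.8% against 14.8% for GEE alone (20 per flat), and 20.5% against 20.4% with unequal flats.

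**Step 6: cost of 6 df.** Interval width for the same standard error: 2.447/1.960 = 1.248. For power, 45 per arm implies a standardised difference of about 0.59. With 82 × 0.7 = 57.4 completers per arm, there are 14.35 per flat, DE = 1 + 13.35 × 0.02 = 1.267 and effective n = 45.3. The non-centrality is 0.59 × √(45.3/2) = 2.81. Power is 80% against the normal reference and 65% against t6.

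**The case against.** The strongest reply is that the article prescribes neither a normal reference nor an uncorrected sandwich. Degrees of freedom, standard-error corrections and the random-effects structure are details that an article commonly leaves to the full protocol or the SAP, which are not shown. That stands: the inflation is conditional on implementation, and the absence of those details is not in itself a fault.

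Three stronger readings are tempting, and the document does not support them.
- A reader might infer that the trial's tests run at 10 to 14% whichever model is used. The mixed model does not: at the planned ICC it is at about 6% even with a normal reference, and it approaches 10% only near an ICC of 0.10.
- A reader might infer that having two p-values to choose from is a further source of false positives. Step 5 shows that it adds almost nothing beyond GEE's own inflation.
- A reader might infer that flats will be left out of the analysis. The section never says so, and randomisation by flat, the ICC in the sample size and the stated adherence to the CONSORT cluster extension point the other way. It is only one possible reading of an unspecific text.

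What the reply does not answer is what the section does fix. It gives a many-cluster method equal standing for eight clusters, names no deciding model and does not identify the cluster. The Discussion's remark about confounding does not address the test.

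**Conclusion.** The concern holds in a limited form. Two methods with different small-cluster behaviour are named for the same comparison, with no priority between them and without flat as the stated cluster. If the GEE route is followed in its standard uncorrected form, the nominal 5% test has a true size of about 14%, and about 20% with the strongly unequal flats assumed here. If flats were ignored, it would be about 8.5 to 10% at ICC 0.02. The mixed-model route is close to nominal: about 6% with a normal reference and about 4% with Satterthwaite df. These figures assume two-sided tests, normally distributed outcomes, a single follow-up time and, in the fitted-model simulation, a baseline-outcome slope of 0.6. The GEE figure hardly depends on the ICC; the others do.

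**What to change.** Name one primary analysis for the continuous outcomes, with flat as the cluster and a small-cluster method. Either of these would do:
- a linear mixed model with random intercepts for flat and participant, adjusted for the baseline value, with Satterthwaite or Kenward-Roger degrees of freedom; or
- a baseline-adjusted cluster-level t-test on 6 df.

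Keep GEE only as a sensitivity analysis, clustered on flat, with a bias-corrected sandwich and a t reference on 6 df. Capping the mixed model at 6 df is not needed, because it is conservative at ICC 0.02 (about 2%).

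A permutation test over the C(8,4) = 70 allocations is optional. Its smallest two-sided p-value is 2/70 = 0.029 and the next is 4/70 = 0.057, so it rejects at 5% only for the single most extreme split.

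The cost is some wording and programming, intervals up to about 25% wider for the same standard error, and some power: on the plan's own assumptions, from about 80% to about 65% with a strict 6-df test before any gain from baseline adjustment. The Study status section reports that baseline measurement was complete and the intervention under way, so the choice should be fixed before outcome data are examined by arm.
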